### Aims of the study

The aims of the study are to assess the feasibility of a cluster randomised controlled trial to compare the performance of an HCA training package in relational care against current training in improving the care of older patients in acute NHS settings, and to explore optimal methods for cost-benefit analysis for a definitive study.

Important parameters that are needed to inform the feasibility of a definitive trial (and if feasible, then the design of such a trial) [28] will be assessed:The acceptability of the intervention to trainers and HCA trainees.The willingness of ward managers, HCAs and older patients to participate in a cluster randomised controlled trial.The willingness of ward managers for wards to be randomly allocated.The level of non-response and item non-response to outcomes at the level of ward, HCA and patient.The acceptability of outcome measures to participants.The ability to monitor levels of resource-use and quality of life data.The variability within and between ward, HCA and patient outcomes.The appropriateness of ward as the unit of randomisation.

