### Recruitment

#### Wards

The ward manager provides permission for ward participation. Recruitment of wards will cease once permission is given by ward managers of 4 eligible wards from each of 3 acute NHS Hospital Trusts (*n* = 12 wards in total).

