### Intervention

#### HCA training in relational care: Older People’s Shoes

HCAs from wards randomised to the new training intervention (*n* = 6 wards, 2 wards per hospital) will receive ‘Older People’s Shoes’, a newly developed HCA training package that focuses on the relational care of older people. The training intervention was developed using evidence from interviews with HCAs, other ward staff, older people, and a panel of experts. The intervention development work was funded by the same grant but in an earlier phase of this project. Course materials comprise a trainer manual and trainee workbook, PowerPoint resources and an online version of the training.

Training will take place during weeks 5 to 8 post-randomisation after the 4-week set-up period. It comprises 2 training days approximately 1 week apart. Older People’s Shoes training is delivered by registered nurses, all of whom are employed at the local Hospital Trust in practice development or education and training roles. These trainers receive full training in the content and delivery of ‘Older People’s Shoes’ from members of the research team.

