#### Wards

Observations by a researcher employed on the grant will take place on the four enrolled wards at each participating NHS Hospital Trust. For each ward, eight observations will take place during the baseline period and eight during the follow-up period. Each observation will last for 50 minutes.

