#### Ward-level analysis

QUIS will be analysed as a total mean rating for each observed session. Analysis will be based on the change from baseline to outcome using a general linear model including NHS Hospital Trust as this was a stratification variable. Due to the small number of wards this analysis will be descriptive.

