#### HCA-level analysis

The outcomes of TEQ and AGED will be assessed using a linear mixed-effect model, with fixed effect being the intervention and the random effect will be ward. This will account for the potential of dependence of HCA-level responses from HCAs within the same ward. Additionally, the baseline value of the outcome will also be included as a fixed effect in a sensitivity analysis. These models will allow the estimation of the parameters required, including the within-ward and between-ward variance, for the planning of future trials, including the HCA-level variation and between-ward variation.

Due to the small number of clusters, the results of the random-effect model will also be compared to those using a generalised estimating equation (GEE) model. Additionally, as the number of clusters is less than 15 per arm [39], sensitivity will be analysed as a total average, per ward, rating as well as the individual sub-types. Due to the small number of wards involved this analysis will be descriptive. Additionally, the sensitivity of the assumption of a normally distributed outcome will be assessed using the two-stage, non-parametric bootstrap.

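### The QUIS analysis does not say whether the eight sessions per ward are collapsed: without a ward term a session-level fit ignores clustering, and a ward-level fit does not return the session variance

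*Protocol article*

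**What the plan says.** The Ward-level analysis section fixes the score: "QUIS will be analysed as a total mean rating for each observed session". It then takes change from baseline to outcome, "using a general linear model including NHS Hospital Trust as this was a stratification variable". Trust is the only model term named. Neither the intervention nor ward appears, and nothing says whether sessions are averaged within ward first. The section closes: "Due to the small number of wards this analysis will be descriptive".

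On the design, the Sample size section says "For each ward, eight observations will take place during the baseline period and eight during the follow-up period". Recruitment stops at "4 eligible wards from each of 3 acute NHS Hospital Trusts". Allocation is by ward, six to each arm and two per arm in each Trust.

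The Aims of the study list, among the parameters needed for a definitive trial, "The variability within and between ward, HCA and patient outcomes". The opening of the Statistical analysis section puts the emphasis on estimating parameters for a future sample size and on differences with confidence intervals. The HCA-level and patient-level sections each specify a random ward effect and say that those models will supply the variance estimates. The HCA-level section also says that "sensitivity will be analysed as a total average, per ward, rating as well as the individual sub-types", without naming the outcome.

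**The concern.** Sessions on one ward share staff, patients and routines, so their ratings are likely to be correlated. The ward is what was randomised. A linear model fitted to session ratings without a ward term treats up to 96 values per period as independent when there are 12 independent units.

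Baseline and follow-up sessions are not described as matched. A change per session therefore needs either an arbitrary pairing or a ward baseline mean shared by all eight follow-up sessions. The section settles neither this nor the unit.

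Two things are at stake. One is the interval for the QUIS difference, if it is computed at session level. The other is the set of variance components for the definitive trial, which inform the balance between sessions per ward and number of wards. QUIS is the only one of the three outcome levels whose stated model has no route to those components.

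**Working it through.** The documents give no SD, ICC or power figure for QUIS, so there is no stated figure to reproduce. Every ICC below is an assumption.

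**Inputs from the protocol article.** 12 wards; 3 Trusts; 6 wards per arm, 2 per arm per Trust; 8 sessions per ward per period. Sessions per period: 12 × 8 = 96. Total: 192. The intervention term is assumed to be in the model.

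**Notation.** Session variance is set to 1. ρ is the share due to ward within a period. π is the correlation of a ward's effect between the two periods. Stable ward differences cancel in a change.

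**True variance of the arm difference in change.** A ward's change in mean has variance 2ρ(1−π) + 2(1−ρ)/8. With 6 wards per arm:

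V = (2/6)[2ρ(1−π) + (1−ρ)/4]

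**Reading A: sessions as the unit, no ward term.** The fit claims 96 − 4 = 92 residual df (t = 1.986). At ward level there are 12 − 4 = 8 (t = 2.306).

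Take first π = 0, so that the ward effect is drawn afresh in each period. With arbitrary pairing the naive variance is (2/48) × 2 = 1/12, against V = (1/12)(1 + 7ρ). The design effect is therefore 1 + 7ρ. Simulated coverage of a nominal 95% interval (10,000 trials per row, no true effect):

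| ICC | Design effect | Effective sessions of 96 | Paired arbitrarily | Ward baseline mean subtracted | 12 ward changes |
|---|---|---|---|---|---|
| 0 | 1.00 | 96.0 | 95% | 86% | 95% |
| 0.01 | 1.07 | 89.7 | 95% | 84% | 95% |
| 0.05 | 1.35 | 71.1 | 91% | 80% | 95% |
| 0.10 | 1.70 | 56.5 | 87% | 75% | 95% |
| 0.20 | 2.40 | 40.0 | 78% | 66% | 95% |
| 0.30 | 3.10 | 31.0 | 71% | 60% | 95% |

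Now let ward effects be partly stable (π > 0). A session-level arm-by-period fit without ward has naive variance of about 4/48 = 0.0833:

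- ρ = 0: V = (1/3)(0.25) = 0.0833; SE ratio, naive to true, 1.00.
- ρ = 0.1, π = 0.8: V = (1/3)(0.04 + 0.225) = 0.0883; ratio √(0.0833/0.0883) = 0.97.
- ρ = 0.2, π = 0.5: V = (1/3)(0.20 + 0.20) = 0.1333; ratio 0.79.

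The two variances are equal when 2(1−π) = 1/4, that is π = 0.875. Above that value the session-level arm-by-period fit is conservative. Simulated coverage is 83 to 84% at ρ = 0.3, π = 0.5 and 97% at ρ = 0.3, π = 1.

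Subtracting the ward baseline mean gives naive variance (2/48)[2ρ(1−π) + (9/8)(1−ρ)]. The SE ratios at the same three settings are 0.75, 0.71 and 0.59. The 0.75 at ρ = 0 comes from reusing one baseline mean eight times; no ward effect is involved.

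**Reading B: collapse to 12 ward changes, Trust and arm.** Coverage is about 95% throughout. The model returns one residual variance on 8 df, estimating 2ρ(1−π) + (1−ρ)/4. Ward-by-period and session variance cannot be separated from that one number, and the stable ward variance has cancelled out. The 192 ratings do hold the session variance: 7 df in each of 24 ward-periods, so 24 × 7 = 168 df. The section does not say that it will be calculated.

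**The case against.** The best defence is that the section already means a ward-level analysis. Its heading says so, its reason for description is the number of wards, and change from baseline is natural only per ward because sessions are not paired. The phrase about each session can then be read as a scoring rule that averages coded interactions into one rating. On that reading the comparison of arms is valid. The analysis is also descriptive, no formal test is planned, PEECH is primary, and the pilot is not powered for superiority.

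Much of this stands. A reader might infer that the QUIS interval is wrong on any reading. It is not: ward changes on 8 df give nominal coverage. A reader might also infer that the definitive trial would have no basis for choosing sessions per ward. That too goes beyond the text, since the session ratings are collected and the variance can be calculated from them. SE ratios of 0.75 to 0.59 apply only to subtraction of a shared baseline mean, which the article does not describe.

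What remains is that the only unit named is the session, that intervals and design parameters are planned for the study as a whole, and that the QUIS section, unlike the other two, neither includes ward nor promises variance components. The per-ward average in the HCA section does not close the gap. It is not tied to QUIS, and if it does refer to QUIS it is the collapsed analysis of Reading B.

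**Conclusion.** The point holds as an under-specified analysis with a different cost on each reading. At session level without ward, coverage runs from about nominal (ICC near 0 with paired sessions, or very stable ward effects) to roughly 70 to 85% at larger ICCs, and to 60% in the worst case examined with a shared baseline mean. A session-level arm-by-period fit can also be slightly conservative. At ward level the treatment interval is sound, and the loss is only that the stated model does not deliver the within-ward variance named in the aims.

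The sizes rest on assumed values of ρ and π, on normal errors, and on an intervention term that the section leaves unnamed. Because the analysis is descriptive and QUIS is not primary, this is a worthwhile improvement and no threat to the pilot's main conclusions. The documents do not establish that the per-ward and sub-types sentence is misplaced QUIS text. QUIS does have interaction categories, which makes the inference tempting, but the sentence sits under TEQ and AGED and names no outcome.

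**What to change.** In the Ward-level analysis section, state the unit and choose one of two routes.

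1. Fit a linear mixed model to the session ratings, with arm, period, arm by period and Trust as fixed effects and random ward and ward-by-period effects. Base inference on the 12 wards. Trust in a change-score model corresponds to Trust by period here. With that term the arm-by-period contrast has 12 − 4 = 8 df; with Trust as a main effect only it has 12 − 2 = 10. Using 8 matches the ward-change analysis.
2. Analyse the 12 ward-mean changes with arm and Trust on 8 df, and report the session, ward-by-period and ward variance components separately.

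With balanced sessions the two routes give the same treatment estimate. In the HCA-level section, say which outcome the per-ward average and sub-types sentence refers to.

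The cost is wording and a little more analysis; no data collection changes. The interval will usually be wider than that of a session-level fit that ignores ward. The ward-level components will be imprecise: on 8 df, the 95% limits for a variance are 8/17.53 = 0.46 and 8/2.18 = 3.67 times its estimate, and this should be reported with them.

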#### HCA-level analysis

The outcomes of TEQ and AGED will be assessed using a linear mixed-effect model, with fixed effect being the intervention and the random effect will be ward. This will account for the potential of dependence of HCA-level responses from HCAs within the same ward. Additionally, the baseline value of the outcome will also be included as a fixed effect in a sensitivity analysis. These models will allow the estimation of the parameters required, including the within-ward and between-ward variance, for the planning of future trials, including the HCA-level variation and between-ward variation.

Due to the small number of clusters, the results of the random-effect model will also be compared to those using a generalised estimating equation (GEE) model. Additionally, as the number of clusters is less than 15 per arm [39], sensitivity will be analysed as a total average, per ward, rating as well as the individual sub-types. Due to the small number of wards involved this analysis will be descriptive. Additionally, the sensitivity of the assumption of a normally distributed outcome will be assessed using the two-stage, non-parametric bootstrap.

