#### Healthcare assistants

At baseline, HCAs receive a self-completion questionnaire containing the Assessment of Work Environment Schedule (AWES), [30, 31] the Toronto Empathy Questionnaire (TEQ) [32], and the Age Group Evaluation and Description (AGED) inventory [33]. The 34-item AWES measures HCA perception of the support provided in the work environment. The TEQ conceptualises empathy as an emotional process and contains 16-items, each a statement about empathetic responses to specific situations with which the HCA respondent is asked to rate on a 5-point scale their agreement. The AGED inventory measures the extent to which stereotypes about ageing are held by the respondent. It includes 28 semantic differentials relating to a specific age group (70 years and over) using a 7-point Likert scale.

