### Allocation for trial interventions

Stratified by NHS Hospital Trust, 12 wards will be randomly allocated by the Norwich Clinical Trials Unit. Each ward has an equal chance of receiving either training for HCAs in relational care or training as usual. Random allocation is generated via computer-written code. To conceal allocation from those responsible for recruitment, randomisation takes place immediately after baseline measures are completed and 4 weeks ahead of the start of the intervention (set-up period) to allow appropriate arrangements including HCA cover.

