#### Healthcare assistants

HCAs will receive the TEQ and AGED inventory twice during the follow-up period, at weeks 9 and 12 post-randomisation.

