#### HCAs

All eligible HCAs will be invited to take part. Numbers of HCAs employed on wards varies within and between NHS Hospital Trusts. Assuming approximately 10 HCAs employed on each enrolled ward, and an estimated recruitment rate of 70 %, it is anticipated that 84 HCAs will be recruited (42 per arm). A total of 12 HCAs from the intervention arm will be invited to take part in a semistructured interview. Anticipating that there will be some shortfall between recruitment to training and uptake of training, this number represents approximately one third of expected trainees. Requesting interviews with a greater number would put undue strain on ward staffing levels. Of those HCA trainees who give initial consent to interview, purposive sampling will be used to select across NHS Hospital Trusts, and to maximise variation of interviewees in terms of gender and length of experience.

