### Statistical analysis

Within the analysis plan, the emphasis will be on the estimation of parameters required for a future sample size calculation and potential differences via confidence intervals, rather than formal hypothesis testing.

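### The main TEQ and AGED model leaves out the HCA's own baseline score, so its confidence interval is wider than it needs to be

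*Protocol article*

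**What the plan says.** All references are to the protocol article.

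- **Baseline.** Under Baseline measures, Healthcare assistants: "At baseline, HCAs receive a self-completion questionnaire containing the Assessment of Work Environment Schedule (AWES"; the same sentence goes on to list the TEQ and the AGED inventory. Under Allocation for trial interventions, wards are randomised once baseline measures are complete, so these scores precede allocation.
- **Follow-up.** Under Outcomes, Healthcare assistants: "HCAs will receive the TEQ and AGED inventory twice during the follow-up period, at weeks 9 and 12 post-randomisation".
- **Main model.** The section on HCA-level analysis opens as follows: "The outcomes of TEQ and AGED will be assessed using a linear mixed-effect model, with fixed effect being the intervention and the random effect will". The sentence closes by naming the ward as that random effect. No baseline term and no Trust term appear.
- **Role of the baseline score.** The same paragraph adds: "Additionally, the baseline value of the outcome will also be included as a fixed effect in a sensitivity analysis".
- **Planning parameters.** The next sentence reads: "These models will allow the estimation of the parameters required, including the within-ward and between-ward variance, for the planning of future trials".
- **Purpose.** Under Statistical analysis, "the emphasis will be on the estimation of parameters required for a future sample size calculation and potential differences via confidence intervals", in preference to formal testing.
- **Other levels.** The ward-level QUIS analysis uses change from baseline and includes Trust, the stratification variable, in its main model. Baseline and follow-up patients come from separate discharge periods, so the plan offers no own-score baseline for PEECH.

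**The concern.** Of the three outcome levels, the HCA level is the one where individuals are followed from before randomisation to after it, so a person's earlier score can be used directly. That score is likely to be the strongest predictor of the follow-up score. Leaving it out of the main model has two consequences.

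1. The interval for the arm difference is wider than the collected data allow.
2. With 12 wards, a chance difference in mean baseline empathy or attitudes between arms is quite likely, and the unadjusted estimate carries it forward.

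The article states this ordering of the two models explicitly, so it is not a detail left to a fuller document. It also sits oddly beside the QUIS analysis, which uses baseline from the start. What is at stake is the precision of the main TEQ and AGED estimates, not the validity of the comparison.

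**Working it through.** **The plan's own figure.** "Assuming approximately 10 HCAs employed on each enrolled ward, and an estimated recruitment rate of 70 %, it is anticipated that 84 HCAs will be recruited". Check: 12 wards × 10 HCAs × 0.70 = 84, which is 42 per arm and 84/12 = 7 per ward. The figure reproduces.

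**Inputs**
- From the article: "Stratified by NHS Hospital Trust, 12 wards will be randomly allocated by the Norwich Clinical Trials Unit", with six wards per arm; m = 7 HCAs per ward.
- Assumed, because the article gives neither: ICC 0.05 (range 0.01 to 0.10) and baseline-to-follow-up correlation r from 0.3 to 0.8.
- Simplifications: total variance set to 1, equal ward sizes, a single follow-up score, no attrition.

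**Formulas**
- Unadjusted variance of a ward mean: V0 = ICC + (1 − ICC)/m.
- Adjusted, if baseline explains only within-ward variation: VA = ICC + (1 − ICC)(1 − r²)/m.
- Adjusted, if baseline explains the same share at both levels: VB = V0(1 − r²).
- Variance of the arm difference: (2/6) × V. The 95% half-width is t(10 df) = 2.228 times its square root.

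**Unadjusted result at ICC 0.05**
- V0 = 0.05 + 0.95/7 = 0.1857.
- SE = √(0.1857 × 2/6) = 0.249 SD.
- Half-width = 2.228 × 0.249 = 0.55 SD.

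**Adjusted results at ICC 0.05**

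| r | VA | Half-width, within-ward only | Half-width, both levels | Narrowing |
|---|---|---|---|---|
| 0.3 | 0.1735 | 0.54 | 0.53 | 3-5% |
| 0.5 | 0.1518 | 0.50 | 0.48 | 10-13% |
| 0.7 | 0.1192 | 0.44 | 0.40 | 20-29% |
| 0.8 | 0.0989 | 0.40 | 0.33 | 27-40% |

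Example at r = 0.7: √(0.1192/0.1857) = 0.80, so 20% narrower; √(1 − 0.49) = 0.71, so 29% narrower.

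**Sensitivity to the assumptions**
- Over ICC 0.01 to 0.10 the narrowing is 3-5% at r=0.3, 7-13% at r=0.5, 15-29% at r=0.7 and 20-40% at r=0.8.
- Trial status reports 112 consenting HCAs, or 112/12 = 9.3 per ward. At ICC 0.05 the within-ward-only figures become 3%, 9%, 18% and 24%; the both-levels figures do not change.

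**Chance imbalance.** If baseline scores have the same ICC, the arm difference at baseline also has SE 0.249 SD. The probability that it exceeds 0.2 SD in either direction is P(|Z| > 0.2/0.249) ≈ 42%. At r = 0.7, a baseline imbalance of 0.25 SD would move the unadjusted estimate by about 0.7 × 0.25 = 0.175 SD.

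**Trust term.** Adding Trust (three sites, two parameters) reduces the ward-level degrees of freedom from 10 to 8. The multiplier rises from 2.228 to 2.306, a factor of 1.035. If Trust explained nothing, this would use up most or all of the 3-5% gain at r = 0.3, but only a small part of it at r = 0.5 or above. The table isolates the baseline term.

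**The case against.** **No decision turns on which model is called main.** The adjusted model is prespecified and will be fitted. The pilot is not powered for superiority, formal testing is not the emphasis, and the article sets no threshold for TEQ or AGED. This stands and keeps the point modest. It does not remove it: intervals are a stated emphasis, and the wider one is put first.

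**The unadjusted model keeps every HCA with follow-up data.** A simple adjusted model drops those with no baseline form, which matters in a pilot that studies non-response. This also stands, but it is met by retaining those HCAs in the adjusted model.

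**The gain may be small.** True if r is low: 3-5% at r = 0.3, before any cost of the Trust term.

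**A stronger reading: the variance carried into planning is the wrong one.** A reader might infer that only the unadjusted variance feeds a future sample size and inflates it. The document does not support that.
- The sentence on planning parameters refers to models in the plural, directly after both have been described, so the adjusted variances will be available.
- The unadjusted variance is a legitimate planning quantity; it misleads only if used to size a trial analysed with baseline adjustment.
- The primary outcome is PEECH, and nothing says a definitive trial would be sized on TEQ or AGED.
- The inflation that might be cited, 1/(1 − r²) or 1.3 to 2.8 for r = 0.5 to 0.8, is an upper bound. If only within-ward variance is explained it is V0/VA, or 0.1857/0.1518 = 1.2 to 0.1857/0.0989 = 1.9.

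**Conclusion.** The point holds as one of precision. The main HCA-level analysis sets aside a pre-randomisation score that the trial already collects. At 7 HCAs per ward and an assumed ICC of 0.05, its interval is wider than the adjusted one by an amount that ranges from negligible (r = 0.3) to substantial (r = 0.7 to 0.8). Because r and the ICC are assumed, the direction is secure and the size is not.

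Chance imbalance should not be read as bias: the unadjusted estimate is unbiased under randomisation, and imbalance is part of the sampling error that adjustment reduces. Nor does the plan rely on a wrong planning variance, since it draws variances from both models. It would still help to say that both sets will be reported, so that a future calculation can use the one that matches its analysis. This is a worthwhile, inexpensive improvement, not a fault that undermines the pilot.

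**What to change.** 1. Under HCA-level analysis, make the main TEQ and AGED model a linear mixed model with baseline score, arm and Trust as fixed effects and ward as a random effect. Keep the model with arm and ward only as supportive.
2. State that HCAs with no baseline form are retained, for example by mean imputation of the covariate.
3. Report the within-ward and between-ward variances and the ICC from both models, together with the baseline-to-follow-up correlation.

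No new data are needed and both models are already planned, so the change is one of order and wording. The costs are a rule for missing baseline scores, which is a small downside, and two ward-level degrees of freedom for Trust.

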#### Patient-level analysis

All analysis will be based on the intention-to-treat principle, including all recruited patients from within randomised wards. The total PEECH score will be analysed using a linear mixed-effect model with fixed effect being the intervention and the random effect will be ward in order to account for the potential of dependence of patient-level responses from patients within the same ward. The four subscales will be analysed using the same model. These models will allow the estimation of the parameters required for the planning of future trials, including the patient-level variation and between-ward variation. As with the HCA-level analysis, for the patient-level outcomes we will compare results from the random-effect model with those from a GEE model. The sensitivity of the assumption of a normally distributed outcome will be assessed using the two-stage non-parametric bootstrap.

If appropriate, sensitivity of the results to missing data will be checked via multiple imputation. If appropriate, adjustment for baseline factors will be made.

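### GEE is brought in because wards are few, but 12 wards is where standard GEE is weakest; the ward-average check that suits the design is not stated for the primary outcome PEECH

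*Protocol article*

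**What the plan says.** The analysis model for TEQ, AGED and PEECH is a linear mixed model with intervention as fixed effect and ward as random effect. Three further analyses surround it.

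- **GEE.** At HCA level the stated reason is the number of wards: "Due to the small number of clusters, the results of the random-effect model will also be compared to those using a generalised estimating equation" model. At patient level, by analogy with the HCA level, "we will compare results from the random-effect model with those from a GEE model".
- **Ward averages.** At HCA level only: "as the number of clusters is less than 15 per arm [39], sensitivity will be analysed as a total average, per ward, rating". I read this as an analysis of ward averages. The section calls it descriptive. The patient-level section has no counterpart.
- **Two-stage bootstrap.** It is assigned to distributional shape: "The sensitivity of the assumption of a normally distributed outcome will be assessed using the two-stage non-parametric bootstrap". The HCA section says the same.

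The opening of the statistical analysis section puts the emphasis on parameters for a later sample size calculation and on confidence intervals for differences, not on tests. The Outcomes section names PEECH as primary.

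**The concern.** The robust variance of a GEE is justified by a large number of clusters. With few clusters it is too small on average, and normal limits add to the shortfall. Citing few clusters as the reason to bring GEE in therefore reverses the usual argument: the check is less reliable than the model being checked, for the very reason given for using it. If the GEE interval for PEECH comes out narrower than the mixed-model interval, a reader may take that as reassurance when it is largely an artefact of 12 wards.

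The HCA section also recognises that so few clusters call for a ward-average analysis. The patient section carries over GEE and the bootstrap but not that analysis. On the text as it stands, the primary outcome gets the weaker check and not the sounder one. Since intervals are a main output of this pilot, their coverage matters.

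**Working it through.** **Inputs from the article**

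- Wards: "permission is given by ward managers of 4 eligible wards from each of 3 acute NHS Hospital Trusts", so 4 × 3 = 12.
- Intervention arm: "6 wards, 2 wards per hospital", and the same number in the control arm, so k = 6 per arm. Allocation: "Each ward has an equal chance of receiving either training for HCAs in relational care or training as usual".
- HCAs: "Assuming approximately 10 HCAs employed on each enrolled ward, and an estimated recruitment rate of 70" per cent. Check of the article's figure: 12 × 10 × 0.70 = 84, or 42 per arm, as stated. That is m = 7 per ward.
- Patients: 100 questionnaires at follow-up, 100/12 = 8.33 per ward before non-response.

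**Assumptions.** The article gives no interval level and no ICC. I take 95% and show ICC from 0 to 0.50. Unless noted, wards are of equal size, outcomes are normal and Trust is not fitted, since the HCA and patient models do not name it.

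**1. Standard GEE (robust SE, normal limits)**

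For equal wards the robust variance of an arm mean is Σ(ward mean − arm mean)²/k². The unbiased version divides by k(k − 1). The ratio is (k − 1)/k = 5/6 = 0.833. The difference divided by its unbiased SE follows t on 12 − 2 = 10 df, so

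coverage = P(|t₁₀| < 1.96 × √(5/6)) = P(|t₁₀| < 1.789) = 89.6%.

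No ICC enters. Simulation (20,000 runs per setting, m = 7 and 8) gave type I error of 9.8 to 10.6%, that is, coverage of 89.4 to 90.2%. The closed-form SE agreed with a fitted exchangeable GEE.

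**2. The alternatives, same simulation, m = 8 (coverage of nominal 95% intervals)**

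| Assumed ICC | GEE, normal limits | Mixed model, normal limits | Mixed model, t₁₀ | Ward means, t₁₀ |
|---|---|---|---|---|
| 0 | 89.5% | 95.7% | 97.8% | 94.9% |
| 0.01 | 89.8% | 95.6% | 97.5% | 95.1% |
| 0.05 | 89.7% | 94.0% | 96.5% | 95.1% |
| 0.10 | 89.7% | 93.1% | 95.9% | 95.3% |
| 0.20 | 89.7% | 92.3% | 95.2% | 95.0% |
| 0.50 | 89.7% | 92.2% | 95.0% | 95.0% |

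The mixed model covers more than 92.2% at low ICC because the between-ward variance is then often estimated as zero. GEE is below the mixed model in every row. With equal wards, GEE with a Kauermann-Carroll correction and t₁₀ limits is identical to the ward-mean t analysis. The Mancl-DeRouen correction with t₁₀ gave type I error of 3.3 to 3.6%, slightly conservative. A smaller simulation with unequal wards (mean 8.3, ICC 0.05, 1,500 runs) gave 88.3% for uncorrected GEE, 95.3% for ward means with t and 95.7% for Mancl-DeRouen with t.

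**3. Two-stage bootstrap without shrinkage**

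With total variance 1, let b = ICC (between wards) and w = 1 − ICC (within). Resampling wards and then people gives

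bootstrap variance / true variance = [(5/6)(b + w/m) + ((m − 1)/m)(w/m)] / (b + w/m).

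For m = 8.33 and ICC 0.05: b + w/m = 0.05 + 0.95/8.33 = 0.164. The second term is 0.88 × 0.114 = 0.1003. The ratio is (0.1367 + 0.1003)/0.164 = 1.445, and its square root is 1.20.

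| Assumed ICC | 0.01 | 0.05 | 0.10 | 0.20 | 0.30 | 0.50 |
|---|---|---|---|---|---|---|
| Bootstrap SE / true SE | 1.28 | 1.20 | 1.14 | 1.06 | 1.01 | 0.96 |

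The data here are exactly normal, so none of this departure reflects non-normality.

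**The case against.** **The article does not say that GEE will be uncorrected.** This stands. It names no variance estimator, reference distribution or bootstrap variant, and a fuller analysis plan, which is not at hand, could specify a correction. The 90% figure describes the standard form only. What does not depend on that silence is the stated reason for choosing GEE and the absence of the ward-average check from the patient section.

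**GEE is only a comparison, and the few-cluster problem was noticed.** Also true: the mixed model is the main analysis, and the ward-average analysis at HCA level shows awareness. But that awareness is not carried to PEECH.

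**It is a pilot without formal tests.** The variance components, which matter most for planning, come from the mixed model and are untouched. This limits the consequence but does not remove it, because intervals for differences are a declared output.

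**Stronger readings that the article does not support**

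- A reader might infer that GEE and the bootstrap are paired small-cluster remedies that err in opposite directions. The bootstrap is assigned to the normality assumption, and its direction depends on ICC. In simulation its type I error was 1.2 to 3.6% at ICC up to 0.10, about 4 to 6% at 0.15 to 0.20, and 8 to 9% at 0.50.
- A reader might infer that PEECH has no analysis valid in small samples. None is stated, but the planned mixed model with t limits would be adequate.
- A reader might quote GEE coverage of 85.2% with Trust fitted, from P(|t₈| < 1.96 × √(8/12)). The HCA and patient models do not name Trust as a term.

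**Conclusion.** The point holds at moderate weight. The reason given for GEE is the wrong way round: with 6 wards per arm, its standard form covers about 90% in place of 95% at any ICC, below the mixed model with normal limits at about 92 to 96%. The ward-average analysis, which with t limits covers about 95%, is stated for the HCA outcomes but not for PEECH.

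The GEE figure assumes no small-sample correction. It is exact for equal wards, and the one unequal-ward simulation was slightly worse. The mixed-model range depends on the unknown ICC.

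The bootstrap point is secondary. Without shrinkage, it does not isolate departure from normality: its SE is about 28% too large at ICC 0.01, about right at 0.30 and slightly too small at 0.50.

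**What to change.** 1. Make a comparison of ward means with t limits (10 df, or 8 df if Trust is fitted) the small-cluster check, and state it for PEECH as well as TEQ and AGED.
2. Remove the few-clusters rationale for GEE. Either drop GEE as that check, or keep it only with a Kauermann-Carroll or Mancl-DeRouen standard error and t limits.
3. Report the mixed model with small-sample degrees of freedom (for example Satterthwaite or Kenward-Roger).
4. Specify the shrinkage-corrected two-stage bootstrap, so that a difference from the model says something about distributional shape.

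**Cost.** Changes of wording and standard software options, with no new data and a little more analysis work. Intervals will be wider than uncorrected GEE would give. With equal wards the critical values on the unbiased SE are 2.228 against 1.789, so a ward-mean t interval is about 25% wider (2.228/1.789 = 1.245). That is the width needed for the stated coverage.
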